## 8. STATISTICAL ANALYSIS

### 8.1 Descriptive statistics

Descriptive statistics will be provided for all normal distributed variables in the form of mean scores (and standard deviations) before and after the intervention on each of the assessment instruments. Descriptive statistics of variables that are not normally distributed will be represented as median scores and interquartile range will be used. Special attention will be given to numbers and characteristics of participants resigning from the study.

### 8.2 Analysis

The effect of the training on long term victimization (primary study parameter) and on general long term outcomes, will be investigated by means of a repeated measures fixed-effects analysis of variance (ANOVA). The effect on risk factors of victimization (second study parameter) will be tested using multilevel modelling with the pre- and posttest and follow-up on the first level and training condition on the second level (o.a. Snijders & Bosker, 2000). A model will be constructed for every dependent variable and the dependent variables will be adjusted for covariates. Statistical analysis will be conducted using the IBM SPSS Statistics package. Dummy variables will be constructed for every level and the statistical significance of the regression-effects will be tested using the T-test. The dummy-variables and their interaction will be added to the model as fixed effects. The level of significance is set at  $p < 0.05$ , two-sided.

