### Objective:

The proposed study aims to investigate the effects of a psychomotor assertiveness training by means of a multicentre randomized controlled trial (RCT). Effects will be examined at the behavioural level by means of questionnaires and interviews, and at the cerebral level with an fMRI task. The effect on actual victimisation will be investigated as a long term outcome, because the prevalence of incidents is low thus we expect that effects of the intervention will only be visible after a longer period of time. Short term effects on risk factors of victimization (e.g. social cognition, self-stigma, assertiveness, self-esteem, aggression regulation, social behaviour) will be examined, since these are direct targets of the intervention. We expect that the risk factors will mediate the effect between the training and victimization.

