**Main study parameters/endpoints**

Primary study outcome is the long term effect of the psychomotor assertiveness training with elements of kickboxing on victimization, as measured by two questionnaires which examine whether an individual has been victim of a crime. We expect that this effect will be mediated by risk factors of victimization (e.g. social cognition, internal stigma, assertiveness, self-esteem, aggression regulation, social behaviour), as measured by both behavioural and cognitive measures such as interviews, questionnaires and a neuropsychological test, and cerebral measures such as fMRI paradigms. Secondary long term outcome measures are quality of life, recovery, social participation, negative symptoms and coping with trauma.

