## 2. OBJECTIVES

In preparation of the proposed multicentre randomized controlled trial (RCT), the psychomotor assertiveness training was tested in a feasibility study (n=23, dossier number NL49520.042.14, ABR number 49520). Subsequently, the intervention protocol has been evaluated and improved. The proposed study aims to investigate the effects of a psychomotor assertiveness training by means of a multicentre randomized controlled trial (RCT). Effects will be examined at the behavioural level by means of questionnaires and interviews, and at the cerebral level with an fMRI task. The effect on actual victimisation will be investigated as a long term outcome, because the prevalence of incidents is low thus we expect that effects of the intervention will only be visible after a longer period of time. Short term effects on risk factors of victimization (e.g. social cognition, self-stigma, assertiveness, self-esteem, aggression regulation, social behaviour) will be examined, since these are direct targets of the intervention. We expect that the risk factors will mediate the effect between the training and victimization.

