#### **4.1 Sample size calculation**

Sample size was calculated using the computerprogram SPSS Sample Power. In order to find a medium effect size (0.50) with two-sided  $\alpha=0.05$ , power=0.80 and taking 25% drop-out into account, 60 participants per group are needed. This means a total sample size of 120 participants.

Sample size in fMRI studies is usually not determined by power analyses, but by experiences with similar protocols. Exact power calculations are difficult because of the complex 'mass univariate' nature of brain imaging data as well as the difficulty to estimate effect sizes in different regions of interest beforehand. Previous studies suggest that in general, 20 participants are necessary per group to achieve sufficient power and acceptable reliability (Monti, 2011; Thirion et al., 2007). Therefore, in the fMRI-part of the proposed study, 22 participants will be included per group.

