They will be instructed to hand in the device at the following appointment. Patients who are also interested in participating in the MRI sub-study and meet the additional MRI criteria, are asked for a pretest MRI session. During this appointment of approximately 90 minutes participants will perform two tasks in an MRI scanner. After the pretest(s), participants will either receive the psychomotor assertiveness training consisting of 20 weekly training sessions (treatment-group) or befriending sessions (control-group). The last session, participants again receive an accelerometer. They will be instructed to hand in the device at the post assessment. Within two weeks after the last intervention session, a posttest assessment will take place. The appointment will take approximately 180 minutes. With patients who also participate in the MRI sub-study, a posttest MRI session will be planned. After six months, participants will be contacted again for a follow-up assessment consisting of questionnaires similar to the earlier pre- and posttest assessment. Respectively, a year and two years later, participants will be contacted for a second and third follow-up assessment. These assessments will take approximately 110 minutes and consists of an interview and questionnaires. More details about the selection and pre- and posttest instruments can be found in paragraph 5.1. Table 5 shows the study design of the instruments (see appendix F for instruments). The selection assessment, pre- and posttest assessments, follow-up assessments with questionnaires and the intervention sessions will take place at the mental health care institutions. The MRI sub-study will take place at the Neuroimaging Centre in Groningen.

Table 5: study design of the instruments

| Instruments                                      | Pre-selection | Selection | Pre-assessment | Post-assessment | Follow-up I | Follow-up II | Follow-up III |
|---------------------------------------------------------|----------------------|------------------|-----------------------|------------------------|--------------------|---------------------|----------------------|
| Selection criteria evaluated by onsite therapist        | x                    |                  |                       |                        |                    |                     |                      |

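### The primary question is the long-term effect on victimization, but section 8.2 names no waves, deciding term or contrast for the ANOVA that is to answer it

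*Protocol*

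**What the plan says.** The Summary (Main study parameters/endpoints) defines the primary outcome by its time frame: "Primary study outcome is the long term effect of the psychomotor assertiveness training with elements of kickboxing on victimization". The reason given under Objective is that incidents are rare, so "we expect that effects of the intervention will only be visible after a longer period of time".

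Table 5 (section 6.3) schedules both victimization instruments, IVM and CTS2, at five waves: pre-assessment, post-assessment and follow-ups I, II and III. Section 6.3 places post within two weeks of the last session and the first follow-up after six months. It then says: "Respectively, a year and two years later, participants will be contacted for a second and third follow-up assessment".

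The only analysis named for the primary outcome is in section 8.2: "victimization (primary study parameter) and on general long term outcomes, will be investigated by means of a repeated measures fixed-effects analysis of variance". The multilevel model in the next sentence is for the risk factors. The sample size section begins "In order to find a medium effect size (0.50) with two-sided" alpha of 0.05. It does not say to which wave or comparison the 0.50 applies.

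**The concern.** A repeated-measures ANOVA with two groups and several waves gives a group main effect and an omnibus group-by-time interaction. Neither is the long-term difference between arms. The main effect averages over every wave entered, including baseline. The interaction has no direction and reacts to a difference at any wave. With no deciding term or contrast fixed, the protocol does not say which result would answer its primary question, and the candidates can disagree on the same data.

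The wave labels make this harder to settle. Section 3 and the IVM description in section 6.1.2 count two post-tests and two follow-ups. Sections 6.3 and Table 5 have one post-assessment and three follow-ups. The six-month visit is therefore a post-test in one place and a follow-up in another, so a reader cannot tell from the label whether it counts as long term.

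**Working it through.** **The plan's own figure.** The protocol gives 60 per group for an effect of 0.50, two-sided 0.05, power 0.80 and 25% drop-out. A two-sample comparison needs 63 per arm (64 by the exact t calculation), or 84 to 86 after dividing by 0.75, so the 60 does not reproduce. That is a separate matter. Here I use only the number of completers it implies: 60 × 0.75 = 45 per arm.

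**Inputs.** From the protocol: n = 45 per arm, effect 0.50 (SD 1), two-sided 0.05, T = 5 waves in the order pre, post, I, II, III. Assumed: normal scores, compound symmetry, correlation r = 0.3, 0.5 or 0.7, and all five waves in the ANOVA. Let δ_t be the arm difference at wave t and δ̄ its mean over waves.

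**Omnibus group-by-time test.** Noncentrality λ = (n/2) Σ(δ_t − δ̄)² / (1 − r), on 4 and 352 df.
- Post only, δ = (0, 0.5, 0, 0, 0): δ̄ = 0.1 and Σ = 0.16 + 4 × 0.01 = 0.20.
- Sustained, δ = (0, 0.5, 0.5, 0.5, 0.5): δ̄ = 0.4 and Σ = 0.16 + 4 × 0.01 = 0.20.
- In both cases λ = 22.5 × 0.20 / (1 − r) = 6.43 / 9.00 / 15.00, so power is 0.49 / 0.66 / 0.89.

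The two patterns give opposite answers to the primary question, yet the test treats them identically: in each, one wave differs from the other four by 0.5. By the same symmetry, an effect at post and follow-up I only and an effect at follow-ups II and III only both give 0.69 / 0.85 / 0.98.

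**Group main effect.** λ = (n/2) T δ̄² / (1 + 4r), on 1 and 88 df.
- Effect at II and III only, δ̄ = 0.2: λ = 4.5 / (1 + 4r) = 2.05 / 1.50 / 1.18, power 0.29 / 0.23 / 0.19.
- Sustained effect, δ̄ = 0.4: power 0.81 / 0.68 / 0.58.
- Post-only effect, δ̄ = 0.1: significant in 0.11 / 0.09 / 0.08 of trials.

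**One named contrast: baseline-adjusted mean of follow-ups II and III.** Residual variance = (1 + r)/2 − r² = 0.56 / 0.50 / 0.36. The noncentrality is 0.5 × √22.5 / √variance = 3.17 / 3.35 / 3.95 on 87 df.
- Effect of 0.50 at both waves: power 0.88 / 0.91 / 0.97.
- Post-only effect: significant in 5% of trials.

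**Follow-up III alone, baseline-adjusted.** Residual variance = 1 − r² = 0.91 / 0.75 / 0.51; power 0.69 / 0.77 / 0.91.

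**Simulation check** at r = 0.5 (4,000 trials per scenario): interaction 0.656 for post-only and 0.655 for sustained; main effect 0.219 for the late-only effect; interaction under the null 0.049.

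**The case against.** The strongest reply is that the time frame is not wholly open. The IVM description ties the interest in the long term to the two follow-up assessments, gives those a one-year recall, and gives both post assessments six months. Under that count the two follow-ups are Table 5's II and III. Table 5 fits: the questionnaire and task measures of the risk factors stop at follow-up I, while victimization and the secondary long-term outcomes continue to II and III. This stands. A reader might infer that the protocol gives no indication of what long term means; that goes too far. The indication is implicit, however, the labels contradict it elsewhere, and section 8.2 does not use it.

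A reader might also infer that a purely short-term effect can win the trial. The protocol does not support that as a flat statement. Section 8.2 lists no waves, so five waves is an inference, and the short-term positives arise mainly through the interaction. If only pre, II and III were entered, a post-only effect would be significant in about 5% of trials. An effect that had gone by follow-ups II and III would also not meet the Summary's definition of the outcome, whatever the omnibus p-value.

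Nor does the protocol support a tripled false-positive rate. That needs a free choice among five tests (main effect, interaction, and follow-ups I, II and III singly), a menu the protocol never offers. As an upper scenario, that choice gives about 15 to 18% under the null in my simulation (40,000 trials per correlation). A choice between single tests at II and III gives about 8 to 10%. One interaction test fixed in advance holds 5%.

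The gain in power should not all be credited to naming the contrast. An interaction on pre, II and III alone has power 0.53 / 0.68 / 0.89 for an effect of 0.50 at both late waves. Much of the rise to 0.88 / 0.91 / 0.97 comes from adjusting for baseline and averaging two waves.

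Finally, an SAP may specify the contrast. Model detail can be left there, but the time point of the primary endpoint belongs in the protocol. Section 8.3 does name a group-by-time test for the fMRI part.

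**Conclusion.** The point holds in this form: section 8.2 fixes a method without the waves, the deciding term or the contrast needed to answer a question defined by its time frame, and the conflicting labels prevent a reader from filling the gap with certainty. On the natural five-wave reading, the omnibus interaction cannot separate a post-only effect from a sustained one (0.49 / 0.66 / 0.89 for both). The main effect is weak for an effect confined to follow-ups II and III (0.29 / 0.23 / 0.19), the pattern closest to the protocol's stated expectation.

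The sizes rest on 45 per arm, an effect of 0.50, normal scores, compound symmetry and the assumed correlations. The equality of the two interaction powers follows from the algebra under compound symmetry and does not depend on the value of r. The missing specification itself depends on none of these assumptions. It remains with a single instrument and complete data.

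**What to change.** 1. Reconcile the wave labels in section 3, section 6.1.2 (IVM), section 6.3 and Table 5, so that each visit has one name and one recall window.
2. In section 8.2, name one primary contrast: the baseline-adjusted difference between arms in victimization over follow-ups II and III combined, as a 1-df two-sided test at 0.05 from the longitudinal model. Using baseline as a covariate rather than a response also suits the IVM's five-year baseline window.
3. State that the group main effect, the omnibus interaction and the single-wave differences are supportive and cannot establish the primary claim.
4. Tie the 0.50 in the sample size section to this contrast.

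Follow-up III alone is an acceptable alternative if named in advance, at lower power (0.69 / 0.77 / 0.91).

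The cost is wording only, with no added patients or visits. The one loss is that an effect confined to post or follow-up I can no longer be claimed as primary, which agrees with the stated objective. The change should be made before any outcome data are seen by arm.

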#### 6.5 Replacement of individual participants after withdrawal

Participants who withdraw from the study, will not be replaced.. Participants who withdraw from the study will still be invited for post-treatment assessment and follow-up.

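### The repeated-measures ANOVA named for long-term victimisation does not target the long-term effect, mixes unequal IVM recall windows and, as usually run, drops participants with a missed visit

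*Protocol*

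**What the plan says.** Protocol 8.2 states that the effect on long-term victimisation, called the primary study parameter, and on the general long-term outcomes "will be investigated by means of a repeated measures fixed-effects analysis of variance (ANOVA"). The next sentence says that the effect on risk factors "will be tested using multilevel modelling with the pre- and posttest and follow-up on the first level". The software is given only as a package: "Statistical analysis will be conducted using the IBM SPSS Statistics package".

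Other sections bear on how this would work:

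- **Waves.** Table 5 (section 6.3) schedules both primary instruments, the IVM and the CTS2, at the pre-assessment, the post-assessment and follow-ups I, II and III.
- **Recall.** Section 6.1.2 sets the IVM window at five years at baseline, six months at both post assessments and one year at follow-up. I read the two post assessments as the post-assessment and follow-up I.
- **Frequency.** The Summary explains that victimisation is a long-term outcome "because the prevalence of incidents is low". Section 1 cites one-year figures of 16% to 33% for violent crime and 47% for any crime.
- **Missing visits.** The sample size was set "taking 25% drop-out into account", and section 6.5 adds: "Participants who withdraw from the study will still be invited for post-treatment assessment and follow-up".
- **Non-normal variables.** These are mentioned only for descriptive statistics (section 8.1).

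**The concern.** The method does not match the question in three respects.

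1. **Target.** The primary question is the long-term group difference. A group-by-time test over five waves asks whether the arms differ in any pattern of change, and it spreads its degrees of freedom over early and late waves alike. It gives no single long-term effect estimate.
2. **Scale.** With a recall window that is ten times longer at baseline than at the post-assessment, raw IVM scores shift between waves for reasons unrelated to treatment, and the baseline scores have much the largest spread. ANOVA has no term for exposure time.
3. **Missing visits.** Classical repeated-measures ANOVA keeps only participants with all waves. One missed visit removes a person's other data, including data that section 6.5 arranges to collect after withdrawal. If missing a visit depends on earlier victimisation differently in the two arms, the comparison is biased.

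At stake is whether the primary analysis can detect a worthwhile reduction and give an interpretable estimate of it.

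**Working it through.** **The plan's own figure.** For d = 0.50, two-sided alpha 0.05 and power 0.80, two independent means need 2 × (1.960 + 0.842)² / 0.50² = 62.8, so 63 per arm (64 by the t-test). Dividing by 0.75 gives 84 to 86 per arm, against the stated 60. An unstated pre-post correlation could explain the difference: ANCOVA with r = 0.55 gives 44 evaluable and 59 recruited per arm. That is a separate matter and is not used as evidence here. What matters is that 60 per arm with 25% drop-out leaves 60 × 0.75 = 45.

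**Participants with every wave**

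- Drop-out only: 45 of 60 per arm, the best case.
- Assuming also that 5% miss each of three earlier visits: 60 × 0.75 × 0.95³ = 38.6, about 39 per arm.
- Alternatively, with no separate drop-out and each of four post-baseline visits missed independently by 5%, 10% or 15% (assumed): 60 × 0.95⁴ = 49, 60 × 0.90⁴ = 39, 60 × 0.85⁴ = 31.

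**What the omnibus test compares.** With five waves and two arms, group by time has (5 − 1) × (2 − 1) = 4 degrees of freedom. Assume one incident a year. The expected control-arm IVM counts under the protocol's windows are then 5, 0.5, 0.5, 1 and 1. A halved rate makes the last four 0.25, 0.25, 0.5 and 0.5. Group differences of 0.25 to 0.5 are therefore tested against error that is dominated by the five-year baseline count.

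**Power simulation.** The protocol gives no count mean or dispersion, so all of these are assumptions: Poisson counts with lognormal rates, mean one a year, rate ratio 0.5 at every post-baseline wave, 45 complete participants per arm. I re-ran it with a between-person log-SD of 0.8 and 1.2 and a within-person log-SD of 0.4, and the results agreed with the table to within a few percentage points.

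| Test | Windows | Power |
|---|---|---|
| Group-by-time ANOVA, uncorrected | equal, one year | 28–31% |
| Group-by-time ANOVA, uncorrected | protocol's | 13–14% (type I error about 12%) |
| Group-by-time ANOVA, Greenhouse-Geisser | protocol's | 5–7% |
| Linear model on FU II+III, baseline as covariate | both | 59–84% |
| Robust count model on FU II+III, baseline as covariate | both | 68–86% (type I error 6–10%) |

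Another run with equal windows put the omnibus ANOVA at 18–24%, so its level depends on the assumed variation. The ordering does not.

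**Where the loss arises.** The linear model in the fourth row assumes normal errors too, yet it recovers most of the power. A separate simulation used negative binomial counts at one-year prevalences of 16%, 33% and 47%, with 45 per arm. Skewness was 1.7 to 2.9. A plain comparison of means kept type I error at 0.03 to 0.05, with power 0.13 to 0.50 at a halved rate, against 0.12 to 0.53 for a negative binomial model.

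**Attrition bias.** This used five waves, a within-person correlation of 0.5, no true effect, and drop-out in one arm depending on the last observed score (assumed log-odds 0.5 to 1.0 per SD), which left about 75–78% completers. The complete-case estimate at the last wave was off by −0.06 to −0.14 SD; a likelihood model using all visits was off by 0.00. When drop-out did not depend on the score, the two methods were about equally precise (SD of the estimate 0.203 and 0.198).

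**The case against.** Several points count against a stronger version of this criticism.

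- **The test is inferred.** Section 8.2 names no group-by-time F-test for victimisation and does not say that all five waves enter. Its later sentences, on a covariate-adjusted model for every dependent variable with dummy variables and t-tests, could be read as covering the primary outcome and giving single-degree-of-freedom contrasts. This stands: the omnibus test is the usual reading of a repeated-measures ANOVA, not a stated one. Even on the other reading, no long-term contrast is named.
- **Listwise deletion is not stated.** It belongs to the classical procedure. SPSS can also fit a repeated-measures fixed-effects model to incomplete series, so a reader may not take the deletion as given.
- **A reader might infer that about 36% of participants would be excluded** (1 − 38.6/60). That figure rests on an assumed 5% of intermittent misses. The documents support only the 25% planning figure, and section 6.5 may reduce it.
- **A reader might infer that skewed or rare data are the main fault and that a count model cures it.** The results above do not support this: most of the gain comes from the contrast and baseline adjustment. Nor is rare a safe word beside the cited 16–47% a year; many zeros (53–84% of people in a year) describes it better.
- **The recall-window point applies to the IVM.** Section 6.1.2 gives the CTS2 no window by wave. The CTS2 is also an ordered 1-to-8 frequency scale, so a count model with an exposure offset does not carry over to it.
- **For permanent drop-out, a mixed model adds little precision at the last visit.** This also stands. Its advantages are the use of intermittent data and protection against drop-out that depends on observed scores.

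None of this makes the omnibus ANOVA a good choice for the stated question, and it cannot be set aside as a detail for the analysis plan, because the protocol itself names the method.

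**Conclusion.** The point holds in a limited form. The protocol gives its primary outcome a less suitable method than the one it gives the risk factors. On the usual reading, the ANOVA tests all waves together, includes a baseline measured over a different window, and uses only complete series.

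Under the assumed counts, its power for a halved rate is about 28–31% with equal windows and 13–14% with the protocol's (5–7% after correction), against roughly 59–86% for a baseline-adjusted long-term contrast. These figures depend on the assumed mean, dispersion and effect, and on the omnibus reading of section 8.2. They already allow for 45 per arm, so they do not depend on how missed visits are handled.

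The loss of participants is at least 25% if the planned drop-out occurs and complete series are required. Any larger loss, and the 0.06–0.14 SD bias, are conditional on assumed missingness. It should be fixed, but the documents do not support calling the primary analysis invalid because of non-normality.

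**What to change.** Reword section 8.2 for the primary outcome:

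- Analyse the post-baseline visits of all randomised participants with a longitudinal mixed model or GEE that keeps partial series.
- Include baseline as a covariate. For the IVM use, for example, log(count + 0.5) or baseline yes/no, because a log rate is undefined at zero. Add site, gender and fMRI participation, which section 6.2 already promises to adjust for.
- For the IVM use a count link with log recall time as offset, or a logistic model if it is scored yes/no. For the CTS2 use a model suited to its ordinal frequency score.
- Name in advance one long-term group contrast, for example over follow-ups II and III, and say how missed visits are handled.

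**Cost.** No new data or visits, and SPSS has suitable procedures. Choosing the contrast is a design decision that the investigators must make before seeing outcome data. The IVM result becomes a rate or odds ratio instead of a mean difference. Convergence must be checked, and so must small-sample type I error, since the robust count test ran at 6–10% in simulation.

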#### 6.1.4 Covariates

To see what factors influence the results, demographic and biographic variables and substance use will be included in the assessment (Table 3). Alcohol and drugs use is measured before and after the intervention in case something changes during the treatment. Substance use is measured with the “Screening risico op verslavingsproblemen” (Spijkerman, Hendriks, van der Gaag, 2011) and consist of eleven questions regarding how much alcohol and drugs the participant uses in one week or month. Questions about gender, family contact, age, medication and residential area are only asked at baseline. .

Table 3: covariates

| Parameter         | Instrument          | Duration   | Type        |
|-------------------|---------------------|------------|-------------|
| Alcohol drugs use | Screening
Risico | 10 minutes | Self-rating |

|                                                                                 |                            |            |                                 |
|---------------------------------------------------------------------------------|----------------------------|------------|---------------------------------|
|                                                                                 | Verslavingsproblemen       |            |                                 |
| -Gender
-Family contact
-Age
-Medication
-Safety residential area * | Biographical questionnaire | 10 minutes | Open questions and rating scale |

\* based on neighbourhood crime statistics from IVM obtained from the police department.

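### The risk-factor models treat the pretest as one more response rather than as a covariate, so the training effect is a difference in change scores and is estimated less precisely than the same data allow

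*Protocol*

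**What the plan says.** Protocol section 8.2 analyses the risk factors, which it calls the second study parameter, by "multilevel modelling with the pre- and posttest and follow-up on the first level", with training condition on the second level. Dummies are built for every level, and "The dummy-variables and their interaction will be added to the model as fixed effects". The dependent variables are also to be adjusted for covariates, which 8.2 does not list.

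Section 6.1.4 describes the covariates: "demographic and biographic variables and substance use will be included in the assessment". Its table gives alcohol and drug use, gender, family contact, age, medication and safety of the residential area. Section 6.2 adds a correction for the randomisation factors: site, gender and participation in the fMRI substudy. Neither place names the pretest score of the outcome.

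Table 5 in section 6.3 shows ZECV, ISMI, SERS-SF, SIG and Faux pas all measured at pre-assessment, post-assessment and follow-up I.

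**The concern.** When the pretest is a response and condition has a main effect, the model estimates a separate baseline mean for each arm. The condition-by-posttest term is then the pre-to-post change in one arm minus the same change in the other. Randomisation makes the two baseline means equal in expectation, so the extra baseline parameter only adds noise. A chance difference at pretest enters the effect estimate with full weight, whereas a covariate would give it only the weight that the pre-post correlation supports.

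Precision is at stake for the scales that the protocol names as direct targets of the training and as mediators of its effect on victimization. The pretest scores needed to recover it are already collected.

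**Working it through.** **Inputs.** From the section on sample size calculation: effect size 0.50, two-sided alpha 0.05, and "power=0.80 and taking 25% drop-out into account, 60 participants per group are needed". Completers per arm: 60 × 0.75 = 45. Rho is not in the protocol, so it is an assumption and is varied. I take 0.50 to be in units of the raw SD, which is also an assumption.

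**The plan's own figure.** A plain two-group t-test with these inputs needs 64 completers per arm, and 64/0.75 = 85.3, so 86 per arm and not 60. The stated inputs therefore do not reproduce the 60, and it cannot show on which scale the 0.50 was meant. That is a separate matter; here only the 45 completers and the 0.50 are used.

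**Variances (unit SD, n per arm, equal variances, equal correlation rho within person).**

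- As written: Var = 4(1 − rho)/n, which is (2/n) × 2(1 − rho).
- Baseline-adjusted: Var = 2(1 − rho²)/n, which is (2/n) × (1 − rho²).
- Ratio: 2(1 − rho)/(1 − rho²) = 2/(1 + rho), above 1 for every rho below 1.

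Generalised least squares on the three-occasion model agrees. At rho 0.5 and n = 45 the posttest effect has variance 4 × 0.5/45 = 0.0444 with a free baseline difference, and 2 × 0.75/45 = 0.0333 with a common baseline mean.

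**Power.** Noncentral t, 45 per arm, effect 0.50, 88 degrees of freedom as written and 87 adjusted:

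| rho | factor as written, 2(1 − rho) | factor adjusted, 1 − rho² | variance ratio | power as written | power adjusted |
|---|---|---|---|---|---|
| 0.3 | 1.40 | 0.91 | 1.54 | 51% | 69% |
| 0.5 | 1.00 | 0.75 | 1.33 | 65% | 77% |
| 0.6 | 0.80 | 0.64 | 1.25 | 75% | 83% |
| 0.7 | 0.60 | 0.51 | 1.18 | 86% | 91% |
| 0.8 | 0.40 | 0.36 | 1.11 | 96% | 97% |

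A comparison of posttest scores alone has factor 1.00 and 65% power. Below rho 0.5 the model as written is therefore less precise than ignoring the pretest.

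**Does the form of the adjustment matter?** Section 8.2 names occasions at level one and condition at level two, and names participants at neither. Suppose the condition main effect were dropped and no participant effect fitted. The condition-by-posttest term then becomes the raw posttest difference, with true variance factor 1.00 at every rho. Against 2(1 − rho) as written, that is no gain at rho 0.5 and a loss above it (1.00 vs 0.60 at rho 0.7, and 1.00 vs 0.40 at 0.8). Entering the pretest as a covariate adjusts for it with or without a participant effect.

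**The case against.** The group-by-time interaction is a standard analysis and is valid under randomisation. A reader might infer that the training effect is biased, or that section 8.2 is in error. The documents do not support that: the contrast is unbiased, and only efficiency is lost. A reader might also carry the point over to victimization, but the primary outcome has its own repeated measures ANOVA in 8.2.

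Model details and the final covariate set are often left to a statistical analysis plan. Section 8.2 does not list its covariates or say which coefficient is the test, and 6.1.4 does not claim to be exhaustive. This has some force: that the pretest is never a covariate is inferred from the two lists. But 8.2 itself fixes the responses, the dummies and the interaction, and the pretest is explicitly among the responses.

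The size is uncertain, and this objection stands. The protocol gives no pre-post correlation. Its only numerical retest figures for these five scales are 0.90 and 0.91 for SERS-SF (section 6.1.2), with no interval stated, and it calls ISMI retest reliability high. If such values held over the course, the gain for those scales would be near zero. The effect size of 0.50 is tied to no scale. If it were meant in change-score SD units, power as written would be 65% at every rho, although the variance ratio would not change. The power figures also ignore clustering in training groups of up to ten, which baseline adjustment does not remove.

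Finally, it is tempting to say that dropping the condition main effect is always equivalent to covariate adjustment and can never lose precision. That needs a participant random effect or within-person covariance, which 8.2 does not state.

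**Conclusion.** The point holds as one of efficiency for the second study parameter. As written, the risk-factor models estimate the training effect as a difference in change scores, with variance 2/(1 + rho) times that of a baseline-adjusted analysis. This identity assumes complete data, equal variances and a random-intercept structure. With drop-out it holds only approximately, but the baseline means remain unconstrained.

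The power gain is about 18 points at rho 0.3, 12 at 0.5 and 5 at 0.7, and under 2 points at 0.8 or more. Which value applies to which scale cannot be settled from the protocol. The change is worth making because the pretest data are already in hand. It does not invalidate the planned analysis.

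**What to change.** In section 8.2, for each risk factor, use posttest and follow-up I as the responses. Enter the pretest score of that risk factor as a covariate interacted with time, include a participant random effect, and report the condition effect at each post-baseline wave.

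Alternatively, keep all three occasions as responses with one common baseline mean for both arms (time dummies plus condition-by-posttest and condition-by-follow-up terms, and no condition effect at pretest). This version should be used only with an explicit participant random intercept or within-person covariance, because without one it does not adjust for baseline.

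The cost is a sentence or two of analysis wording and very few degrees of freedom. No new data, visits or participants are needed.
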